## Abstract

**Background:**

Randomized controlled trials (RCT) on the treatment of severe space-occupying infarction of the middle cerebral artery (malignant MCA infarction) showed that early decompressive hemicraniectomy (DHC) is life saving and improves outcome without promoting most severe disablity in patients aged 18–60 years. It is, however, unknown whether the results obtained in the randomized trials are reproducible in a broader population in and apart from an academical setting and whether hemicraniectomy has been implemented in clinical practice as recommended by national and international guidelines. In addition, they were not powered to answer further relevant questions, e.g. concerning the selection of patients eligible for and the timing of hemicraniectomy. Other important issues such as the acceptance of disability following hemicraniectomy, the existence of specific prognostic factors, the value of conservative therapeutic measures, and the overall complication rate related to hemicraniectomy have not been sufficiently studied yet.

**Methods/Design:**

DESTINY-R is a prospective, multicenter, open, controlled registry including a 12 months follow-up. The only inclusion criteria is unilateral ischemic MCA stroke affecting more than 50% of the MCA-territory. The primary study hypothesis is to confirm the results of the RCT (76% mRS ≤ 4 after 12 months) in the subgroup of patients additionally fulfilling the inclusion cirteria of the RCT in daily routine. Assuming a calculated proportion of 0.76 for successes and a sample size of 300 for this subgroup, the width of the 95% CI, calculated using Wilson's method, will be 0.096 with the lower bound 0.709 and the upper bound 0.805.

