## Background

Severe space-occupying middle cerebral artery infarction (malignant MCA infarction) is a worst case scenario in stroke medicine. Comparable to other devastating subtypes of stroke such as severe intracranial hemorrhage and basilar artery thrombosis therapeutic options are limited and questionable with respect to improved outcome. Even under maximum intensive care treatment most patients die after only few days due to relentless edema formation, brain tissue shift and transtentorial herniation
[1-3]. In contrast, decompressive hemicraniectomy (DHC) has been proven a life saving surgical intervention. Its efficacy in malignant MCA infarction has been demonstrated in three randomized controlled trials (RCT), their a pooled-analysis, and a recent meta-analysis: Early DHC within 48 hours significantly reduces mortality and improves the chance of surviving with mild to moderate disability without increasing the risk of most severe disability
[4-7].

Although the RCT and the two analyses gave answer to the most pertinent question, they were not powered for other important issues: First, due to the strict inclusion criteria of the RCT, only healthy and independent young patients (18–60 years) were treated. In addition, a positive treatment effect was only found within 48 hours after stroke onset
[4-7]. Therefore, it is unclear if the results can be extrapolated to real world situations, when co-morbidities and dependency are common and the decision to proceed with decompressive surgery is made later on in the course of the disease. Second, since the RCT were not powered for adequate subgroup analysis - only 109 patients were included in the latest meta-analysis, 58 underwent DHC and 51 were treated conservatively
[4]- it remains unclear which individual patients benefit from surgical decompression, e.g. with respect to age, presence of aphasia, and timing of surgical intervention. Moreover, it remains unclear which clinical or radiolgical factors sufficiently predict edema formation and thus allow selection of patients for DHC in advance of clinical deterioration
[8-12]. Third, with respect to the extent of the infarction and the unrealistic expectation of complete recovery after severe stroke, “favorable” outcome was defined as a score of ≤ 4 on the modified Rankin scale (mRS) in the pooled-analysis of the RCT
[7]. It is a matter of ongoing debate amongst experts if such a condition may be classified as “favorable”

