[13]. Indeed, some authors and the latest meta-analysis defined favorable as a mRS of ≤ 3
[4]. Other authors think that the question of favorable (or in such severe diseases rather “acceptable”) outcome should be answered by the patients themselves. Unfortunately, the contradictory data on quality of life and retrospective consent to hemicraniectomy after malignant MCA infarction that are currently found in the literature are of little help in preoperative decision making
[5,9,14-18]. Fourth, the actual effectiveness of conservative treatment has never been addressed in detail, e.g. the RCT showed different outcomes in the conservative treatment groups: patients who were treated on an intensive care unit
[5] had a higher rate of survival (47% vs. 22%) and more often better functional outcome (mRS 0–4: 33% vs. 0%) than patients treated on a stroke unit or a general ward
[6]. Fifth, despite the life-saving character of DHC, the overall case fatality rate in patients who underwent surgery in the RCT was still 29%
[7]. This means that nearly every third patient dies for reasons not well understood. Similarly, no valid data are available on the actual rate of complications especially concerning re-implantation of the skull.

Most of these issues are a commonplace in the scientific community and have been addressed in a number of case series and non-randomized case control studies
[19-21]. However, most of these studies are retrospective in nature, lack appropriate control groups, and show heterogeneous or inconclusive results. Therefore, proper investigation in a large-size, prospective study is urgently needed. Besides, the implementation of hemicraniectomy in clinical practice has not been reviewed since the publication of the RCT.

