### Outcome measures

The primary outcome measure is functional outcome as determined by the mRS score, dichotomized between 0–4 and 5 or 6 at 1 year ± 14 days after symptom onset in the subgroup of patients additionally fulfilling the inclusion criteria of the RCT. Secondary outcome measures are: (a) mortality, (b) median time of survival assessed by the Kaplan-Meier estimator, (c) functional outcome as determined by the mRS Score dichotomized between 0–3 and 4–6 at 1 year ± 14 days after symptom onset, (d) treatment modes (i.e. osmotherapy, hyperventilation, sedation, etc.), assessed at discharge if applicable, time to decompressive surgery, diameter of bone flap/craniectomy measured in situ and by neuroimaging, type of duraplasty, if applicable, as well as complications (i.e. hygroma, impaired wound healing, epidural and subdural hematoma, parenchymatous hematoma, wound and bone flap infections) and (f) time to cranioplasty assessed 1 year ± 14 days after symptom onset if applicable, other complications (i.e. pneumonia, and any other infection, thrombosis, seizures), (g) quality of life determinded by the SF-36 and EuroQoL-5D questionnaires and depression assessed by the HDRS, and (h) rate of retrospective consent to treatment assessed 1 year ± 14 days after symptom onset.

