### Sample size calculation

Assuming a calculated proportion of 0.76 for successes in the subgroup of patients additionally fulfilling the inclusion cirteria of the RCT, and a sample size of 300 for this subgroup, the width of the 95% CI, calculated using Wilson's method, will be 0.096 with the lower bound 0.709 and the upper bound 0.805
[22]. Given an estimated enrolement of 4 patients per center/year at 45 study centers plus one year of follow-up, data acquisition would be concluded in 3 years. Thus the end of the study is planned for 2014.

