The primary outcome measure is functional outcome after 1 year determined by the mRS score and dichotomized between 0–4 versus 5–6. This endpoint was chosen to ensure comparability with the results of the pooled analysis of the RCT. Secondary outcome measures were chosen following the aforementioned open questions that could not be answered in the RCT or have not been conclusively answered in clinical studies yet. They furthermore allow subgroup analyses, e.g. elderly patients, dominant-hemispheric infarction, and timing of treatment, some of which are currently under investigation in accompanying studies
[25].

The assessment of prognostic factors will lead to a better understanding of the risk of malignant infarct swelling and will aid clinical decision-making. We do not claim to assess causative associations in a cohort study. However, we expect to find predictive associations that will be of value in the immediate treatment process as well as in raising new hypotheses for subsequent treatment studies
[26].

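### The 76% benchmark for mRS 0–4 and the 29% surgical case fatality cannot both describe the operated RCT patients at 12 months, and the protocol does not reconcile them

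*Protocol article*

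**What the plan says.** The Abstract (Methods/Design) gives the benchmark: "The primary study hypothesis is to confirm the results of the RCT (76% mRS" of 4 or less after 12 months), to be confirmed in registry patients who also meet the RCT inclusion criteria. The section Sample size calculation uses the same value: "Assuming a calculated proportion of 0.76 for successes in the subgroup of patients" concerned. With 300 patients it reports a Wilson 95% interval of 0.709 to 0.805, width 0.096.

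The section Outcome measures defines the primary endpoint as "functional outcome as determined by the mRS score, dichotomized between 0–4 and 5 or 6 at 1 year ± 14 days". Death, mRS 6, is therefore a failure.

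The Background, citing reference 7, states that "the overall case fatality rate in patients who underwent surgery in the RCT was still 29" per cent. The following sentence repeats the message: "This means that nearly every third patient dies for reasons not well understood". The same reference is cited earlier in the Background for the definition of a favorable result: "outcome was defined as a score of ≤ 4 on the modified Rankin scale (mRS) in the pooled-analysis of the RCT". The Discussion says of the primary endpoint: "This endpoint was chosen to ensure comparability with the results of the pooled analysis of the RCT".

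**The concern.** Being alive with mRS 0–4 and being dead are mutually exclusive, so the two percentages for one group of patients at one time cannot exceed 100% together. Here they do.

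The 76% is the only benchmark for the primary hypothesis and the only proportion used in the precision calculation. If 29% fatality is right for operated patients at 12 months, the benchmark is at least 5 points too high for them, and a registry that reproduced the RCT would tend to look worse than the RCT. If 76% is right for them, fatality was at most 24%. The Background then overstates the mortality reference, and mortality is the first secondary outcome.

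**Working it through.** **Inputs**
- Benchmark P(mRS ≤ 4) = 0.76 (Abstract; Sample size calculation).
- Surgical case fatality = 0.29 (Background, reference 7).
- Success is mRS 0–4, failure is mRS 5 or 6 (Outcome measures).
- n = 300, two-sided 95% Wilson interval (Sample size calculation).
- Conservative groups compared in the Background: mRS 0–4 in 33% and 0%.
- Meta-analysis in the Background: 58 operated and 51 conservative patients, 109 in total.

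**1. The plan's own interval.** With z = 1.96, the Wilson limits are
[p + z²/(2n) ± z·√(p(1 − p)/n + z²/(4n²))] / (1 + z²/n).

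At p = 0.76 and n = 300: (0.7664 ± 0.0488)/1.0128 = 0.709 to 0.805, width 0.096. This matches the protocol. The interval arithmetic is correct, so the question concerns the input.

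**2. Consistency.** P(mRS ≤ 4) = 1 − P(mRS 5) − P(death) ≤ 1 − 0.29 = 0.71. The benchmark is 0.76, and 0.76 + 0.29 = 1.05.

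**3. Rounding.** The smallest values that round to the printed figures are 75.5% and 28.5%. Their sum is 104%, still before any mRS 5.

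**4. Could 76% refer to all RCT patients?** The Abstract does not name an arm. Take the ceiling of 71% for surgery and the higher quoted conservative rate, 33%, for every conservative patient. With the meta-analysis split, the overall rate is at most (0.71 × 58 + 0.33 × 51)/109 = 58.01/109 = 53%. To reach 76% overall, the conservative rate would have to be (0.76 × 109 − 0.71 × 58)/51 = 41.66/51 = 82%. The split is not critical: an average of a rate of at most 71% and a rate of at most 33% stays at or below 71% under any weighting. The one assumption is that the third RCT's conservative group, whose result is not given, did not do far better than the two quoted.

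**5. Could the time points differ?** The Background gives none for the 29%. If it refers to a time before 12 months, the conflict grows, because deaths only accumulate. Deaths counted beyond 12 months, or a different set of patients, could reconcile the figures. The document states neither.

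**6. Size of the effect if 29% is right.** At p = 0.71 and n = 300: (0.7164 ± 0.0517)/1.0128 = 0.656 to 0.758, width 0.102, which excludes 0.76.

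Summing exact binomial probabilities over all counts whose Wilson interval excludes 0.76:

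| True rate | P(interval excludes 0.76) |
|---|---|
| 71.5% | 0.446 |
| 71% | 0.522 |
| 70% | 0.668 |
| 68% | 0.881 |

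The first row is the ceiling if 29% was rounded up from 28.5%. The lower rows correspond to 1 or 3 per cent of patients surviving with mRS 5.

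**The case against.** The strongest reply is that the protocol never says that the two figures share a source and a patient set. The Abstract gives 76% without arm, denominator or citation, and the sample size section calls it a calculated proportion; the only citation there follows the Wilson interval. The 29% has an arm and a citation but no time point. The Discussion says that the endpoint was chosen to match the pooled analysis, not that 76% was taken from it. This stands. A reader might infer that one of the two numbers must be false, but the document does not support that: both could be correct for different patients or times and merely be badly labelled.

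A reader might also convert the percentages to patients: 76% and 29% of 58 are about 44 and 17, together 61. That adds no evidence, because the 58 operated patients belong to the meta-analysis, whereas the 29% is cited to the pooled analysis.

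A third tempting inference is that a registry reproducing the RCT could not reach the target. That goes too far. At a true rate of 71%, about 48% of registries would still have an interval that includes 0.76. No success criterion is tied to the interval either: the sample size section plans precision, the analysis is descriptive, and the Discussion says that a registry can only generate hypotheses.

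Finally, the effect on precision is small. Moving from 0.76 to 0.71 widens the interval by 0.006, and no target width is stated from which 300 was derived.

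These points limit the consequences. They do not remove the conflict between the printed figures, which no passage resolves.

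**Conclusion.** The point holds in this form: as presented, 76% with mRS 0–4 at 12 months and 29% case fatality cannot both describe the operated RCT patients at 12 months. The discrepancy is at least 5 percentage points, and larger if any survivor had mRS 5. Neither rounding nor an all-patients reading explains it, the latter under the assumption stated in step 4. Which figure is at fault, or whether they describe different patients or times, cannot be settled without the cited source.

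It matters because 76% is the sole reference value for the primary hypothesis. The 52% chance of an interval excluding 0.76 rests on 29% being right, no mRS 5 survivors and 300 evaluable patients. It describes how the result would tend to look, not a failed test. Nothing here calls for a different sample size.

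**What to change.** Check both figures against the cited pooled analysis. For each, state the arm, numerator, denominator, time point and citation, and correct the one that is wrong.

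- If the benchmark changes, restate the primary hypothesis in the Abstract and the interval in the Abstract and the sample size section. At p = 0.71 and n = 300, for example, the interval would be 0.656 to 0.758, width 0.102.
- If only the 29% is wrong, correct the Background, including the sentence that restates it as nearly one patient in three. The benchmark and interval stay as they are.
- If both are right for different patient sets or time points, say so where each is given, and say why the 76% is the suitable comparison for the registry subgroup.

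The cost is one source check and a text correction. Recruitment, data collection and sample size are unaffected.

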**Discussion:**

The results of this study will provide information about the effectiveness of DHC in malignant MCA infarction in a broad population and a real-life situation in addition to and beyond RCT. Further prospectively obtained data will give crucial information on open questions and will be helpful in the plannig of upcomming treatment studies.

**Trial registration:**

(ICTRP and DRKS): DRKS00000624

## Background

Severe space-occupying middle cerebral artery infarction (malignant MCA infarction) is a worst case scenario in stroke medicine. Comparable to other devastating subtypes of stroke such as severe intracranial hemorrhage and basilar artery thrombosis therapeutic options are limited and questionable with respect to improved outcome. Even under maximum intensive care treatment most patients die after only few days due to relentless edema formation, brain tissue shift and transtentorial herniation
[1-3]. In contrast, decompressive hemicraniectomy (DHC) has been proven a life saving surgical intervention. Its efficacy in malignant MCA infarction has been demonstrated in three randomized controlled trials (RCT), their a pooled-analysis, and a recent meta-analysis: Early DHC within 48 hours significantly reduces mortality and improves the chance of surviving with mild to moderate disability without increasing the risk of most severe disability
[4-7].

Although the RCT and the two analyses gave answer to the most pertinent question, they were not powered for other important issues: First, due to the strict inclusion criteria of the RCT, only healthy and independent young patients (18–60 years) were treated. In addition, a positive treatment effect was only found within 48 hours after stroke onset
[4-7]. Therefore, it is unclear if the results can be extrapolated to real world situations, when co-morbidities and dependency are common and the decision to proceed with decompressive surgery is made later on in the course of the disease. Second, since the RCT were not powered for adequate subgroup analysis - only 109 patients were included in the latest meta-analysis, 58 underwent DHC and 51 were treated conservatively
[4]- it remains unclear which individual patients benefit from surgical decompression, e.g. with respect to age, presence of aphasia, and timing of surgical intervention. Moreover, it remains unclear which clinical or radiolgical factors sufficiently predict edema formation and thus allow selection of patients for DHC in advance of clinical deterioration
[8-12]. Third, with respect to the extent of the infarction and the unrealistic expectation of complete recovery after severe stroke, “favorable” outcome was defined as a score of ≤ 4 on the modified Rankin scale (mRS) in the pooled-analysis of the RCT
[7]. It is a matter of ongoing debate amongst experts if such a condition may be classified as “favorable”
[13]. Indeed, some authors and the latest meta-analysis defined favorable as a mRS of ≤ 3
[4]. Other authors think that the question of favorable (or in such severe diseases rather “acceptable”) outcome should be answered by the patients themselves. Unfortunately, the contradictory data on quality of life and retrospective consent to hemicraniectomy after malignant MCA infarction that are currently found in the literature are of little help in preoperative decision making
[5,9,14-18]. Fourth, the actual effectiveness of conservative treatment has never been addressed in detail, e.g. the RCT showed different outcomes in the conservative treatment groups: patients who were treated on an intensive care unit
[5] had a higher rate of survival (47% vs. 22%) and more often better functional outcome (mRS 0–4: 33% vs. 0%) than patients treated on a stroke unit or a general ward
[6]. Fifth, despite the life-saving character of DHC, the overall case fatality rate in patients who underwent surgery in the RCT was still 29%
[7]. This means that nearly every third patient dies for reasons not well understood. Similarly, no valid data are available on the actual rate of complications especially concerning re-implantation of the skull.

Most of these issues are a commonplace in the scientific community and have been addressed in a number of case series and non-randomized case control studies
[19-21]. However, most of these studies are retrospective in nature, lack appropriate control groups, and show heterogeneous or inconclusive results. Therefore, proper investigation in a large-size, prospective study is urgently needed. Besides, the implementation of hemicraniectomy in clinical practice has not been reviewed since the publication of the RCT.

## Methods

### Study design

DESTINY-R is a prospective, multicenter, open, and controlled registry. There will be no active allocation of the patients either to hemicraniectomy or any conservative treatment option. At the time of publication 45 neurologic and neurosurgical departments were registered as actively recruiting study centers. All participating centers have adequate experience with the management of acute ischemic stroke, intensive care treatment of patients with increased intracranial pressure (ICP) and access to neurosurgical facilities on a 24-hours/day basis.

### Ethics

The study protocol and all subsequent amendments are approved by the leading ethic committee of the Charité- Universitätsmedizin Berlin (Ethic Committee at Campus Benjamin Franklin, Reference number EA4/108/109, date of approval 12/08/09) and the local ethics committees of the participating centers. The study is performed in accordance with the Declaration of Helsinki and its subsequent amendments, as well as the guidelines of Good Clinical Practice. The study is registered at the German Clinical Trial Register (DRKS) and the International Clinical Trials Registry Platform (ICTRP). The registration number is DRKS00000624. Written informed consent is obtained from subjects who meet the study inclusion criteria or their legal representatives, respectively.

### Study subject recruitment

At each study site patients older than 18 years of age are screened and asked for participation if they meet the following inclusion criteria: (a) clinical signs of unilateral MCA infarction, (b) ischemic infarction affecting at least 50% of the MCA territory confirmed by computed tomography (CT) or magnetic resonance imaging (MRI). Additional involvement of the anterior and/or posterior cerebral artery territories may be present, (c) written informed consent of the patient or their legal representative. Because treatment is independent from participation in DESTINY-R there is no time interval for inclusion. The only exclusion criterion is a simultaneous or contemporary acute brain injury, e.g. traumatic brain injury or concomitant infarction contralateral or infratentorial in addition to the index- infarction.

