### Study protocol

After written informed consent is obtained patients are enrolled in the study and baseline data are documented (visit 1). Subsequently, patient’s medical treatment data are recorded throughout the regular treatment. No additional examinations or interventions are carried out by reasons of the study. At discharge medical treatment data are documented in the case-report-form (visit 2). One year after symptom onset patients or their legal representatives are contacted by phone or letter (visit 3). Follow-up data are also documented in the CRF. After completion a copy of the CRF and a compact disc containing the patients’ pseudonymized neuroimaging data is sent to the coordinating center (Center for Stroke Research Berlin (CSB)), which is responsible for data management and analysis.

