### Data analysis

All outcome measures will undergo descriptive data analysis, including mean, standard deviation, median, range, as well as absolute and relative frequencies depending on the scales of the variables. Additionally, descriptive *p*-values for group comparison and the corresponding 95% confidence interval will be indicated. Two-sample *t* testing, the Mann–Whitney *U*-test, or *χ*2-testing will be used to analyze group differences as applicable. Kaplan-Meier estimates and log-rank statistics will be used for assessing cumulative risk of death at 12 months. The comparability of different treatment groups will be depicted by comparing demographic and baseline data. Statistical analysis will be performed using the latest SAS software version (SAS Institute Inc., Cary, NC).

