## Discussion

We advocate the use of a prospective register to further characterize patients with malignant MCA infarction and evaluate implementation, effectiveness and adverse events of current treatment concepts, including DHC. Although first trends in prevalence and outcome of DHC are promising and seem comparable to the results of the RCT
[23,24], the use of a large database allows the representation of a much broader population of patients treated for malignant MCA infarction. The anticipated sample size should allow confirming the results of the RCT and raising new hypotheses even if the population turns out to be more heterogeneous than expected. The planned inclusion of at least 300 patients in a reasonable time frame can only be achieved in a multicenter approach. The open design allows continuing initiation of cooperative study centers. The very conservative estimate of 4 patients/year per center would probably allow extending patient recruitment to 500 or even 1000 if certain questions would need a larger sample size to be investigated. However, due to the nature of a prospective registry, only hypotheses may be created, which then need further investigation in RCT.

To avoid the investigation of a very restricted group of patients, the inclusion criterion of infarct size was intentionally set comparatively wide. Thus any patient with a MCA infarction involving more than 50% of the territory can be included irrespective of treatment, although eligibility criteria for the RCT were infarction of more than 2/3 of the MCA territory. However, as the individual factors promoting infarct swelling are not well understood yet, not considering these patients may possibly exclude a subgroup of patients that would have the potential to benefit from a certain treatment option in the future. The limited number of eligibility criteria are easy to implement even in small hospitals with limited staff and will most likely result in a patient mix representative of clinical practice. Conservatively treated patients are followed simultaneously and constitute the control group, which may be compared to surgically treated patients in this parallel design. Due to treatment bias it may be possible that treatment groups show significantly different baseline data making a true comparison difficult. The expected number of patients should, however, be large enough to compensate for lower event rates or differences in baseline data.

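### Enrolment has no time limit and requires surviving to consent, while the primary outcome runs from symptom onset: early deaths can be missing from the primary proportion, and comparing groups by treatment received gives operated patients immortal time

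*Protocol article*

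**What the plan says.** All references are to the protocol article.

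- **Entry.** Study subject recruitment gives this reason for leaving enrolment open: "Because treatment is independent from participation in DESTINY-R there is no time interval for inclusion". Under Study protocol, a patient is enrolled, and baseline recorded, only once written consent has been given. A legal representative may consent.
- **Clock for the primary outcome.** Outcome measures times the mRS, split at 0–4 against 5–6, "at 1 year ± 14 days after symptom onset in the subgroup of patients additionally fulfilling the inclusion criteria of the RCT". The follow-up contact is also set one year from onset, not from enrolment.
- **When deaths occur.** Background: "Even under maximum intensive care treatment most patients die after only few days due to relentless edema formation".
- **Survival.** A secondary outcome is "median time of survival assessed by the Kaplan-Meier estimator", and Data analysis adds: "Kaplan-Meier estimates and log-rank statistics will be used for assessing cumulative risk of death at 12 months". Neither place names a time origin.
- **Comparison groups.** Treatment is not allocated (Study design). The Discussion says: "Conservatively treated patients are followed simultaneously and constitute the control group". Group differences are tested by t, Mann–Whitney or chi-square tests. Time to surgery is recorded (Data collection).
- **Bias.** The Discussion concedes that treatment bias may make the groups differ at baseline, then says that the expected number of patients should be large enough to compensate.

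**The concern.** The reason given for the open window answers a different question. That treatment does not depend on participation does not make participation independent of survival: a patient must live until consent is obtained. In a disease that kills within days, a registry that may enrol at any later time, but measures outcome from day 0, can over-represent people who got past the dangerous period. The primary aim is to confirm a fixed benchmark, 76% with mRS ≤ 4, so a shift in this proportion bears directly on the conclusion. It could make routine practice appear to match the trials when it does worse.

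The second problem lies in the treatment contrast. A patient counts as operated only after living long enough to reach surgery, and one who dies while waiting counts as conservatively treated. The survival curves, the log-rank test and a chi-square test on the mRS would all then favour surgery even if it did nothing.

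**Working it through.** **1. The plan's own figure.** Wilson 95% interval with p = 0.76, n = 300, z = 1.96:

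- centre = (0.76 + 3.8415/600) / (1 + 3.8415/300) = 0.7567
- half-width = 1.96 × √(0.76 × 0.24/300 + 3.8415/(4 × 300²)) / 1.0128 = 0.0481
- interval 0.7086 to 0.8048, width 0.0963

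This reproduces the stated 0.709, 0.805 and 0.096. The arithmetic of the sample size section is sound.

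**2. Deaths lost before consent.** Let p be the true success proportion among eligible patients and f the share of eligible patients who die before consent. All those lost are failures (mRS 6), so observed success = p/(1−f).

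- To reach the upper bound: f = 1 − 0.76/0.805 = 5.6%.
- For a true value at the lower bound to look like the benchmark: f = 1 − 0.709/0.76 = 6.7%. Per 300 enrolled, that is 300 × 0.067/0.933 ≈ 22 eligible patients never registered.
- From a true 0.70: f = 5% gives 0.70/0.95 = 0.737, and f = 10% gives 0.70/0.90 = 0.778.

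The article gives no onset-to-consent times, so f is an assumption throughout.

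**3. Immortal time with no treatment effect.** From Background: conservative-group survival of 47% and 22%, hence mortality m of 53% and 78%. Assumed: 100 patients intended for surgery and 100 not, with the same mortality; exponential death times with mean μ days among those who die; surgery uniform over 0–2 days; everyone enrolled at onset.

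The share of deaths that precede surgery is q = 1 − (μ/2)(1 − e^(−2/μ)). Then 100mq patients move from the surgical to the conservative group:

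- operated mortality = (100m − 100mq)/(100 − 100mq)
- conservative mortality = (100m + 100mq)/(100 + 100mq)

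| m | μ (days) | q | Operated | Conservative | Spurious gap |
|---|---|---|---|---|---|
| 53% | 3 | 0.270 | 45.1% | 58.9% | 13.7 points |
| 53% | 5 | 0.176 | 48.2% | 57.0% | 8.8 points |
| 53% | 10 | 0.094 | 50.5% | 55.2% | 4.7 points |
| 78% | 3 | 0.270 | 72.1% | 81.8% | 9.7 points |
| 78% | 10 | 0.094 | 76.3% | 79.5% | 3.2 points |

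**4. The two biases together.** Let enrolment be delayed exponentially with mean 1 day, at m = 53%. The chance that a patient who will die does so before enrolment is (1/μ)/(1/μ + 1).

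- μ = 3: this is 0.25, so 0.53 × 0.25 = 13% of all patients are lost, and mortality among those enrolled is (0.53 − 0.1325)/(1 − 0.1325) = 46%.
- μ = 10: it is 0.091, so 5% are lost and mortality is 51%.

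In a simulation of the μ = 3 case, the operated-versus-conservative gap narrows from about 14 points to about 7 (42.1% against 49.1%). It keeps its direction.

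**The case against.** **The loss is possible, not shown.** Representatives may consent, and the Study protocol section describes enrolment first and treatment documentation afterwards, which suggests inclusion in hospital. If consent usually comes within hours, f is small. A reader might infer that the primary proportion is inflated. The article does not support that: it permits the loss but gives nothing from which to size it. What stands is that no limit is set and that the stated reason does not address selection on survival.

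**The trial-criteria subgroup may bring its own time limit.** The article does not list those criteria in full. A limit on when treatment took place would in any case not limit when the patient was registered. Nor does the article say how the randomised trials counted early deaths, so no claim about that is made here.

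**The analysis plan may handle immortal time.** It could; landmark or time-dependent methods are often specified there, and the article does not exclude them. But the methods it names, applied as described, carry the bias. No analysis plan can restore to the mRS proportion patients who were never registered.

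**The Kaplan–Meier origin.** A reader might infer that survival is counted from symptom onset. That is stated only for the mRS outcome and the follow-up contact. Immortal time would also arise with an enrolment origin whenever surgery follows enrolment.

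**The disclaimers.** P-values are called descriptive, causal claims are disowned, and the registry is said only to create hypotheses. This lowers the stakes for the treatment contrast. But the Discussion also expects the sample to allow confirmation of the trial results, and the caveats concern baseline differences, not entry time.

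**Conclusion.** The concern holds, within limits.

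- **Primary outcome.** The design allows eligible patients who die before consent to drop out of a proportion timed from onset. The direction is upward. The size is unknown, but a loss of about 6% of eligible patients would shift the estimate by about as much as the planned interval's half-width (0.048).
- **Treatment contrast.** Grouping by treatment received produces a spurious mortality advantage for surgery of roughly 5 to 14 points at 53% mortality, or 3 to 10 at 78%. This assumes no true effect, surgery within 48 hours, enrolment at onset, and mean time to death of 3 to 10 days. It concerns secondary, descriptive comparisons, not the single-group primary proportion.
- **Not additive.** It is tempting to read both biases as adding up in favour of surgery. In the treatment contrast they partly offset, because late enrolment also removes early deaths counted as conservative.

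More patients would only narrow the interval around a biased value, so the Discussion's reliance on sample size does not answer either problem.

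**What to change.** 1. Keep enrolment open, but define the primary analysis set by a maximum onset-to-enrolment time stated before analysis. Show all enrolled patients as a sensitivity analysis.
2. A window limits the pre-consent loss but does not remove it. State this limit on the comparison with 76% and, where screening records exist, report the number of eligible patients who died before consent.
3. State symptom onset as the origin for survival, and let each patient enter the risk set at enrolment (delayed entry).
4. Compare treatments with hemicraniectomy as a time-dependent covariate, or from a landmark among patients alive and enrolled at that time. For the mRS comparison, use the landmark.
5. Delete the Discussion's statement that the number of patients should compensate for differences between the groups.

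Cost: changes of wording and analysis, plus the enrolment date in the analysis dataset. Time to surgery is already recorded, and the onset and consent dates are needed to run the visits. Patients registered late leave the primary set, so it is somewhat smaller and its confidence interval somewhat wider than planned for 300.
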